### Intervention description {11a}

The patients will be managed according to operating procedures for TUMT and PAE at each centre. Both procedures are conducted under local anaesthesia in the outpatient department. Usually, the patient can be discharged from the hospital on the same day. If the patient cannot be discharged on the same day, he will be admitted to the urological ward. Below is a general description of the two procedures.

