The secondary outcomes include the following:The mean IPSS of the two arms at all other follow-up occasions than the primary outcome.The mean procedure time for the conduction of TUMT and PAE as well as the calculated necrosis.Health-related quality of life measured by the mean IPSS-QoL, BII, and EQ-5D-5L. IPSS-QoL assesses the quality of life associated with symptoms from urinary problems. The BII is a self-reported, validated, disease-specific instrument for quantifying the interference of LUTS on the patient’s mental health and activity. As a measure of QoL, it is used to determine treatment outcomes in men with symptomatic benign prostatic hyperplasia [22]. The EQ-5D is the most widely applied instrument for health-economic assessment worldwide. Its index values are used in the estimation of quality-adjusted life year gains in economic evaluations of healthcare interventions [23].Mean satisfaction with treatment by a five-level bipolar Likert scale.Erectile function measured by the mean IIEF-EF score. The IIEF-EF domain score is a PROM used to measure erectile performance and assess disease severity in efficacy trials. It distinguishes between men with and without erectile dysfunction (ED), classifies levels of ED severity, and has the requisites to detect treatment-related changes in patients with ED [24, 25].Ejaculatory function measured by the mean DAN-PSS-1-sex. The DAN-PSS-1-sex is a validated instrument to determine erectile and ejaculatory function and its impact on the well-being of the patient [26].Incontinence measured by the mean ICIQ-UI-SF. The ICIQ-UI-SF is validated for evaluation of the frequency, severity, and impact on QoL of urinary incontinence [27].Mean prostate volume (PV) measured by TRUS in mL.Mean uroflowmetry outcomes of the two arms. We will be looking at voided volume, Qmax, and residual urine. Uroflowmetry is a non-invasive procedure used to measure the flow of urine throughout micturition. It provides useful information about the total voiding function and is used for diagnosis of lower urinary tract dysfunctions and evaluation of treatment response. Qmax is the value of the highest flow rate measured during the test; it will be set to zero if the patient has an indwelling catheter. Transabdominal ultrasound will be used to assess post-voided residual urine as it is accurate and non-invasive [28].Post-procedure catheterisation events, including the placement of an indwelling urinary catheter and the use of intermittent catheterisation. Catheterisation will be expressed as the reason for placement, duration, and frequency (in case of intermittent catheterisation). If an indwelling catheter is placed after the procedure, the post-procedure duration of catheterisation will be defined as days from the procedure till indwelling catheter cessation. Catheterisation for any other reason during the follow-up period will also be evaluated.Prostate-specific antigen (PSA) and creatinine. The absolute value of serum PSA (ng/mL) has a good predictive value for the determination of prostate volume. Continued PSA measurements assist in the detection of any de novo prostate cancer or progression of patients in active surveillance or watchful waiting. A rise in serum creatinine can be a result of BPH with urinary retention. Serum creatinine aids in the identification of any affection of the kidney from the procedures.De novo use of pharmacological LUTS treatment and surgical re-treatment rates will be collected from the patient’s health record.Incidence at 3 months post-procedure of urinary tract infection, acute urinary retention, dysuria, haematuria, post-embolisation syndrome (PES), hospital admission, and hospitalisation time. PES is defined as occurring within 48 h after surgery and consisting of influenza-like symptoms, pelvic pain, nausea, dysuria, or transient worsening of LUTS. Data on AEs and side effects will be collected from the patient’s health record and the follow-up visit at 3 months. Surgical complications will be categorised following the Clavien-Dindo grading [29].

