##### Follow-up management

Patients will be followed for 5 years post-procedure, with a total of four follow-up visits to the outpatient clinic at 3, 6, 12, and 24 months. The results from the long-term follow-up at 5 years will be completed with digital PROMs and assessment of the patient’s health record. Outcome data will be collected in accordance with Table 1. To complete the procedures and PROMs for the follow-ups at 3 months to 5 years, a 28-day window will be allowed, defined as 14 days before and 14 days after the due date. For the 1-month follow-up, the permitted window will be 10 days, 5 days before and 5 days after the due date.

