### Adverse event reporting and harms {22}

#### Adverse events definition

##### AEs

An AE is any untoward medical occurrence in a patient or to whom a medical product or surgical procedure has been administered, including occurrences that are not necessarily caused by or related to the procedure. The study compares two acknowledged treatments with a known spectrum of side effects. Therefore, the assessment of AEs is not based on spontaneous reporting but on these specific expected AEs occurring from the procedure until the first follow-up (0–3 months). The most common side effects of TUMT include urinary tract infection (0–30% [37]), urinary retention (0–12% [38]), dysuria (0–6.7% [14]), post-procedure haematuria (0–26.8% [14]), haematuria requiring additional treatment (0–1.24% [14]), retrograde ejaculation (0–22.2% [12]), and ED (0–9% [37]). Compared to TURP, men undergoing TUMT are significantly less likely to require blood transfusion and experience retrograde ejaculation [12]. The most common side effects of PAE include urinary tract infection (0–13.8% [39]), late acute urinary retention (0–10% [40]), PES (0–100% [39]), access-site hematoma (2–12% [41]), pseudoaneurysm (0.5 to 6.3% [42]), and ED (0–2% [7]). Major complications following PAE such as non-target embolisation and vessel injury with subsequent bleeding are rare with an overall incidence of 0.5% [43]. Surgical complications will be registered in REDCap by the study personnel and classified using the Clavien-Dindo classification [29].

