#### Adverse event reporting

The REDCap alerts tool will be used to notify the PI when an SAE has been reported in the database. The PI at each centre is responsible for reporting any unexpected SAEs to the ethics committee within 7 days. This report will be accompanied by remarks on any consequences of the trial. Throughout the total study duration, it is also the PIs responsibility to submit annual safety reports to the ethics committee of all serious expected and unexpected side effects and all serious events that have occurred during the period. This report will include an evaluation of the safety of the trial participants. The PI will keep study personnel informed of any safety issues that arise during the trial.

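### The only scheduled enquiry about adverse events is at 3 months, so post-embolisation syndrome, a 48-hour symptom outcome, rests on chart entries or on recall about 75 to 103 days later

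*Protocol article*

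**What the plan says.** Outcomes {12} lists among the secondary outcomes: "Incidence at 3 months post-procedure of urinary tract infection, acute urinary retention, dysuria, haematuria, post-embolisation syndrome (PES), hospital admission, and hospitalisation time". It defines PES as follows: "PES is defined as occurring within 48 h after surgery and consisting of influenza-like symptoms, pelvic pain, nausea, dysuria, or transient worsening of LUTS". It names two sources for these data: "Data on AEs and side effects will be collected from the patient’s health record and the follow-up visit at 3 months".

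The article points to Table 1 for the time points at which secondary outcomes are collected. There the AEs/SAEs row has one mark, at FU 2 (3 months ± 14 days). The Intervention and FU 1 cells are empty. The only row marked at FU 1 (1 month ± 5 days) is the Likert scale. Follow-up management lists clinic visits at 3, 6, 12 and 24 months, so the 1-month contact is not one of the clinic visits. Its window is stated: "For the 1-month follow-up, the permitted window will be 10 days, 5 days before and 5 days after the due date".

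Intervention description {11a} says of both procedures: "Usually, the patient can be discharged from the hospital on the same day". The AEs section says that assessment does not rest on spontaneous reports but on listed expected events, "from the procedure until the first follow-up (0–3 months").

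SAEs have further provisions: a dedicated case report form for 0–3 months and inpatient register data (SAEs section), and an alert (Adverse event reporting): "The REDCap alerts tool will be used to notify the PI when an SAE has been reported in the database".

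**The concern.** PES is made up of symptoms that a man may have at home in the first two days and never report. Same-day discharge puts most of the 48-hour window outside the hospital. If he does not seek care, nothing enters the health record, and the first time anyone is scheduled to ask him is at FU 2. He must then remember the symptom and also place it within 48 hours of the procedure.

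The date affects classification as well as completeness. Dysuria is an outcome in its own right and also a component of PES, and whether an episode can count towards PES depends on when it occurred. The trial is open-label, so each man answers knowing his treatment.

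What is at stake is the comparison of early side effects. Objectives {7} says the secondary comparisons are meant to serve clinicians in counselling patients who are choosing between the two procedures. The non-inferiority test on IPSS at 6 months does not depend on these data.

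**Working it through.** No sample-size or power figure is involved; the check is date arithmetic on the article's own schedule.

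Inputs:
- PES window: 48 h = 2 days (Outcomes {12}).
- FU 1: 1 month ± 5 days; FU 2: 3 months ± 14 days (Table 1).
- Assumption: 1 month = 30 days and 3 months = 91 days, since the article does not give the visits in days.

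The article's own window lengths reproduce: 14 + 14 = 28 days for FU 2 and 5 + 5 = 10 days for FU 1, as Follow-up management states.

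Day of enquiry = nominal day ± window. Lag = day of enquiry − 2.

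| Contact | Earliest day | Latest day | Lag after the PES window closes |
|---|---|---|---|
| FU 2 (the present schedule) | 91 − 14 = 77 | 91 + 14 = 105 | 77 − 2 = 75 to 105 − 2 = 103 days |
| FU 1 (if harms were asked about there) | 30 − 5 = 25 | 30 + 5 = 35 | 25 − 2 = 23 to 35 − 2 = 33 days |

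In weeks, FU 2 falls 77/7 = 11 to 105/7 = 15 weeks after the procedure. Taking 3 months as 90 to 92 days changes the lag only to 90 − 14 − 2 = 74 up to 92 + 14 − 2 = 104 days.

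Two consequences follow for the remedy. Asking at FU 1 alone would shorten recall to 23 to 33 days, which is better but still long for dating a symptom to within 48 hours. A form completed at same-day discharge would miss whatever begins at home. Only a contact shortly after 48 hours matches the definition.

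The means are already described. Plans for assessment and collection of outcomes {18a} sends questionnaires as REDCap links by text message, and section {18b} describes automated distribution with a reminder after 3 days.

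**The case against.** The best reply is that the 3-month visit is not the only source. The health record is named for AEs, and SAEs have their own form, register data and an alert. This is right, and it limits the point to mild symptoms that never reach a record. How many symptoms those are, the article does not say.

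A second reply is that a journal article condenses the protocol, and that discharge forms or entry rules may sit in the full protocol or in the REDCap manual that section {18a} mentions. That would be a full answer if the article were silent. It is not: it gives Table 1 as the schedule for secondary outcomes, and that table has one mark for AEs/SAEs and nothing but the Likert scale at 1 month.

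Several stronger readings are tempting and are not supported:
- *SAEs will reach the ethics committee too late.* The alert does depend on database entry, and no earlier enquiry is scheduled. But the SAE form and register do not wait for FU 2, the 7-day rule covers unexpected SAEs only, and its starting point (occurrence or awareness) is not given. No breach is shown.
- *The safety looks would lack early harms.* Interim analyses {21b} places them at 6-month follow-up, after FU 2.
- *Records are fuller in one arm.* Catheter care after the procedure differs in part between the arms, but men with a permanent catheter before embolisation also keep it until they void. Nowhere does the article say that record-keeping differs, so this is inference.
- *Sites could close the AE window at 1 month.* Calling 3 months the first follow-up clashes with the label FU 1, but the same sentence gives 0–3 months and the SAEs section repeats it. It is a slip of label.
- *The cited PES range of 0–100% shows that ascertainment decides the result.* The article gives it as a literature range and does not attribute it to timing.

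**Conclusion.** The concern holds in a limited form. The schedule, as fixed, asks about harms directly for the first time 11 to 15 weeks after the procedure, and so about 75 to 103 days after the PES window closes. For symptoms that were never charted, the incidence of PES and of early dysuria and haematuria depends on dated recall over that interval by men who know their treatment. These incidences should be regarded as unreliable. Neither the size of the error nor the direction of any bias between the arms can be worked out from the document.

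This rests on reading Table 1 as the complete schedule of enquiry and on months of about 30 days. It does not touch the primary outcome or the sample size, and it does not show a failure of SAE reporting. An earlier checklist would deal with recall; it would not remove the effect of open-label reporting.

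**What to change.** Send the same short symptom checklist, with a date for each symptom, to both arms through the existing REDCap text-message system just after 48 hours and again at FU 1. Keep the FU 2 enquiry and the record review. Mark the two new points in the AEs/SAEs row of Table 1. In the AEs section, have the window end at FU 2 (3 months) so that the label agrees with the table.

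The cost is two added survey forms and a small extra questionnaire burden, with no new visit or staff. Recruitment began in October 2022, so men treated before the change cannot be asked in time. Report the early-harm incidences separately for those treated before and after the change.

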**Screening activities**								
Informed consent	**X**							
Inclusion/exclusion	**X**							
Randomisation	**X**							
Demographics	**X**							
Medical history	**X**							
**Procedures**								
CTA	**X**							
TRUS/MRI (prostate volume)	**X**			**X**	**X**	**X**	**X**	
Blood test (PSA + creatinine)	**X**			**X**	**X**	**X**	**X**	
Uroflowmetry (flow + residual urine)	**X**			**X**	**X**	**X**	**X**	
**Assessments**								
Likert scale			**X**	**X**				
PROMs (IPSS, IPSS-QoL, BII, EQ-5D-5L, ICIQ-UI-SF, IIEF-EF, DAN-PSS-1-sex)	**X**			**X**	**X**	**X**	**X**	**X**
Catheter use	**X**			**X**	**X**	**X**	**X**	
Technical details of the procedure				**X**				
AEs/SAEs				**X**				
Re-treatment rates						**X**	**X**	**X**

*CTA* computed tomography angiography, *TRUS* transrectal ultrasound, *MRI* magnetic resonance imaging, *PSA* prostate-specific antigen, *PROM* patient-reported outcome measure, *IPSS* International Prostate Symptom Score, *IPSS-QoL* International Prostate Symptom Score—Quality of Life, *BII* Benign Prostatic Hyperplasia Impact Index, *ICIQ-UI-SF* International Consultation on Incontinence Questionnaire—Urinary Incontinence Short Form, *IIEF-EF* International Index of Erectile Function—Erectile Function, *DAN-PSS-1-sex* Danish Prostatic Symptom Score—sexual questions, *AE* adverse event, *SAE* serious adverse event

### Participant timeline {13}

#### Screening and inclusion

At the screening visit, the research physician will determine whether the patient is eligible to be included in the study by assessing inclusion and exclusion criteria. At inclusion, baseline data will be obtained following Table 1.

##### Follow-up management

Patients will be followed for 5 years post-procedure, with a total of four follow-up visits to the outpatient clinic at 3, 6, 12, and 24 months. The results from the long-term follow-up at 5 years will be completed with digital PROMs and assessment of the patient’s health record. Outcome data will be collected in accordance with Table 1. To complete the procedures and PROMs for the follow-ups at 3 months to 5 years, a 28-day window will be allowed, defined as 14 days before and 14 days after the due date. For the 1-month follow-up, the permitted window will be 10 days, 5 days before and 5 days after the due date.

### Sample size {14}

A non-inferiority study design was chosen based on several case studies on the efficacy of TUMT and PAE in men with similar inclusion criteria as this trial. From a review of TUMT, a study with a baseline IPSS above 19 and follow-up after 3 months was selected [30]. In this study, the IPSS 12 weeks after TUMT had decreased to 11.3 with a standard deviation (SD) of 6.3 [8]. With PAE, a recent independent study has demonstrated an IPSS at baseline of 19.4 with an SD of 6.3. Twelve weeks after the procedure, the IPSS declined to 10 with an SD of 6.5 [7]. The difference of approximately 1 IPSS point between the two treatments holds for 6- and 12-month follow-up according to the data available in systematic reviews [10, 12, 31]. Due to resource constraints of our trial and the great variation in SD across TUMT and PAE trials, we have chosen an SD of 5 [30, 32]. The sample size calculation was based on “Sample sizes for clinical trials with normal data. *Statist. Med.* 2004; 23:1921–1986” by Julious [33]. The size was calculated using the package “PowerTOST” in R for the sampleN.noninf() function in R set to parallel design. We used a one-sided significance level of 0.025. Power was set at 80%. Assuming a difference in mean IPSS after treatment of + 1 point in the favour of TUMT with an SD of 5 and a non-inferiority margin set at the border for a clinically non-meaningful difference of + 3 points in the favour of TUMT [34, 35], the calculated size was 100 per group, giving a total size of 200 patients. Dropouts are defined as patients who after inclusion are lost to follow-up for the primary outcome. To compensate for an anticipated dropout rate of 10%, the study will include 223 patients.

### Recruitment {15}

The enrolment period is expected to be 3 years. The study will be terminated after the last follow-up of the last patient. The total study duration is expected to be 8 years. Patients will be recruited from the urological outpatient clinics of the participating centres. The treatment-responsible physician will alert the patient when he is selected for MIST BPH treatment. The number of patients treated with either TUMT or PAE in the Capital Region of Denmark every year exceeds the target sample size. As it is a pragmatic trial, most of these patients will be eligible for inclusion. As the enrolment period is 3 years, we expect the flow of patients in the clinic to be sufficient to cover the sample size. By having multiple centres participate in the study, we prevent bias and ensure sufficient inclusion.

## Assignment of interventions: allocation

### Sequence generation {16a}

The study will randomise patients in a 1:1 manner to either Arm 1: TUMT or Arm 2: PAE following a computer-generated randomisation schedule. Randomisation will be performed as block randomisation including blocks of varying sizes with site stratification using the randomisation module in REDCap (Research Electronic Data Capture). Details on block sizes will not be disclosed to ensure the concealment for those enrolling patients.

### Concealment mechanism {16b}

REDCap allocates the patient when baseline measures have been completed and the informed consent signed, in that way the allocation concealment will be guaranteed.

### Implementation {16c}

In this study, we will implement complete separation of the individuals involved in sequence generation and assignment of treatment. The randomisation sequence is generated by the trial statistician who will not be involved in enrolling patients. In this way, randomisation will be conducted without the influence of the PI or trial physicians. The block size will be concealed until the primary endpoint will be analysed. The list will be uploaded to REDCap without the possibility that those enrolling and assigning participants will obtain access to the list.

## Assignment of interventions: blinding

### Who will be blinded {17a}

N/a. This is an open-label trial; both study personnel and patients will be aware of the received treatment. Due to the physical component of the surgical procedures and outcome assessments, blinding of the patients, surgeons, and outcome assessors has not been possible in our setting. The data analyst will be blinded by having an independent statistician who will be blinded to treatment group allocations conducting the analysis.

### Procedure for unblinding if needed {17b}

N/a. This is an open-label trial; both study personnel and patients will be aware of received treatment.

## Data collection and management

### Plans for assessment and collection of outcomes {18a}

Data from assessments and procedures will be collected following Table 1 and Fig. 1. All trial data will be collected in REDCap, a secure web application for building and managing databases and online surveys. Project staff will be trained in completing the REDCap database by the PI and all study groups will follow a REDCap manual for data collection. Predefined definitions for complications and AEs will be specified in the REDCap database to get homogeneous responses for AE outcomes. PROMs will as a first option be distributed to the patients by a REDCap link sent to their phone as an SMS via a secure third-party service. All questionnaires will be included in the same survey string via the auto-continue function in REDCap; this ensures data collection from all PROMs. Data from the questionnaires will be collected in REDCap directly. PROMs and data collection instruments are chosen to be reliable, valid, and have inter-rater reliability with previous randomised clinical trials in BPH research. Most of the instruments used here are included in the registry network for surgical treatment of BPH [20].

**Fig. 1 Fig1:**
[figure not shown]
Trial profile

### Plans to promote participant retention and complete follow-up {18b}

For an improved adherence to follow-up protocol, study benefits and importance will be emphasised at inclusion. A well-functioning, organised, and persistent research team with trained research nurses will have the responsibility of data registration. Surveys are preferably distributed digitally as it has shown a greater adherence [36]. However, the data collection methods can be tailored to the participant’s needs. PROMs can be distributed by text message, e-mail, or paper format and inclusion visits can be facilitated in person and/or by phone. REDCap Automated Survey Distribution Tool will be used to ensure distribution at the right time. This will also send out reminders after 3 days if a survey has not been completed. If questionnaires are still not being filled out, to ensure the primary outcome is completed, the patient will complete the surveys at a visit to the outpatient clinic or will be contacted by the study personnel. Reminders will not be sent to those participants who have completed their survey, opted out, or have been marked as not active in the study.

